**Table 17-1 Sample size calculation for the MD expansion phase**

|                  |                              |                              |                              |                              |                              |
|------------------|------------------------------|------------------------------|------------------------------|------------------------------|------------------------------|
| Active treatment | 60% PASI75                   | 55% PASI75                   | 70% PASI75                   | 70% PASI75                   | 60% PASI75                   |
| Placebo          | 15% PASI75                   | 10% PASI75                   | 20% PASI75                   | 10% PASI75                   | 10% PASI75                   |
|                  | 80%power with 32+16 subjects | 80%power with 30+15 subjects | 80%power with 28+14 subjects | 90%power with 22+11 subjects | 83%power with 26+13 subjects |

## 17.2 Statistical methods

### 17.2.1 Primary endpoint

Primary endpoint for safety is adverse events and observed toxicity to Anti-IL-20 (109-0012) 100 mg/vial administration where the severity is assessed using NCI's CTCAE, version 3. All adverse events with onset after the first administration of trial drug will be included in the analysis.

The adverse events will be analysed using descriptive statistics. The adverse events will be summarised by trial phase (SD dose-escalation, MD dose-escalation or MD expansion phase), dose, MedDRA system organ class and MedDRA preferred term. The summary will additionally be presented by CTCAE grading (severity) and by relation. The descriptive statistics will include the number and percentage of subjects who experienced adverse events, the severity and the number of events. Adverse events will be listed by trial phase, dose and subject with information on severity according to the CTCAE criteria, relationship to trial drug and demographics.

### 17.2.2 Secondary endpoints

#### Efficacy:

- PASI (PASI75 is the primary endpoint for the MD expansion phase)
- PGA
- VAS (assessment of arthritis symptoms for subjects with psoriatic arthritis)
- QoL (MD expansion phase only)

PASI75, 75% reduction in PASI, will be assessed by comparing the measurement from the visit at trial Day 29 in the SD phase, and trial Day 57 in the MD phases, to baseline values measured prior to the first dose. PASI90 will be derived analogously.

PASI, PGA and VAS will be listed by trial phase, dose, and time. Additionally, PASI75 and PASI90 will be summarised by trial phase and dose, and PASI, PGA, VAS and QoL will be summarised by treatment group for the MD expansion phase.

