3. ECG
4. BSA
5. PGA
6. PASI and VAS (if applicable)
7. Haematology
8. Biochemistry
9. Urinalysis
10. Hormones
11. Sampling for molecular biomarkers (baseline)
12. Sampling for serum/plasma biomarkers (baseline)
13. Sampling for antibodies (baseline)
14. Urine pregnancy test (if applicable)
15. Inclusion and exclusion criteria
16. Concomitant medication
17. Adverse events
18. PK sample (0 hours)

Thereafter subjects will be randomised to the lowest number available and receive a subcutaneous injection of either active treatment or placebo into the abdomen. Since the trial is double-blind, neither the subject nor the investigator/study nurse will know whether active treatment or placebo is administered. There is a 3:1 chance of receiving active treatment.

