5. BSA
6. PGA
7. PASI and VAS (if applicable)
8. Sampling for molecular biomarkers will be performed at 24 hours (Day 2) after drug administration.
9. Blood samples for haematology, biochemistry, and hormones will be collected, together with a urine sample, at 24 hours after drug administration.
10. Subjects will be closely monitored for the first 24 hours and any adverse events and/or local irritation at injection site will be registered.
11. Drug accountability will be performed.

After the 24-hour samples have been collected, ECG recording has been performed and blood pressure has been measured, the subject can leave the site.

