### **Day 3 to Day 85**

Subjects will come for regular visits at Day 3, 8, 15, 29, 57 and 85. From Day 29 a deviation of  $\pm 3$  days from the scheduled day will be allowed.

The following data and samples will be collected and recorded at **all visits to site**:

1. Vital signs
2. Haematology
3. Biochemistry
4. Urinalysis
5. Hormones
6. Serum/plasma biomarkers
7. Adverse events
8. Local tolerability
9. Concomitant medication
10. Collection of PK samples

Procedures which are not performed at every visit are listed below, together with the time point at which they should be performed:

Day 8: ECG and sampling for molecular biomarkers.

Day 15: ECG, sampling for molecular biomarkers, BSA, PGA, PASI, and VAS (if applicable).

Day 43 ( $\pm 3$  days): The investigator/study nurse will call all subjects and check their status only (withdrawal criteria, concomitant medication, and adverse events).

Day 57 ( $\pm 3$  days): ECG, BSA, PGA, PASI, VAS (if applicable), sampling for antibodies and body measurements (weight only).

Day 71 ( $\pm 3$  days): The investigator/study nurse will call all subjects and check their status only (withdrawal criteria, concomitant medication, and adverse events).

Day 85 ( $\pm 3$  days): BSA, PGA, PASI, VAS (if applicable).

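### Single-dose PASI75 and PASI90 are read at Day 29, but the visit procedures in Section 8.1.1 list no PASI at that visit

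*Protocol*

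**What the plan says.** Section 4.2 names PASI, with PASI75, as a secondary efficacy endpoint of both dose-escalation phases. Section 17.2.2 gives the time point for the SD phase: "PASI75, 75% reduction in PASI, will be assessed by comparing the measurement from the visit at trial Day 29 in the SD phase". The same sentence uses Day 57 for the multiple-dose (MD) phases. It adds that "PASI90 will be derived analogously", and both responder rates are to be summarised by trial phase and dose.

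Section 8.1.1 sets out the SD visits. For the middle part of follow-up, "Subjects will come for regular visits at Day 3, 8, 15, 29, 57 and 85". It gives one list of procedures for every site visit and then a second list, introduced by: "Procedures which are not performed at every visit are listed below, together with the time point at which they should be performed". On that second list PASI appears at Day 15 ("Day 15: ECG, sampling for molecular biomarkers, BSA, PGA, PASI, and VAS (if applicable"), at Day 57 ("ECG, BSA, PGA, PASI, VAS (if applicable), sampling for antibodies and body measurements (weight only") and at Day 85. It is also listed before dosing on Day 1, during the stay after dosing, and at the last visit on Day 106.

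The Summary says that assessments follow the flow charts as well as Section 8, so Table 2-1 also governs the SD schedule.

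**The concern.** A responder endpoint needs two measurements per subject: baseline and the analysis day. Section 17.2.2 names Day 29 as the analysis day, and Section 8.1.1 does not call for a PASI then. The SAP could change the time point, but it cannot supply a score that nobody recorded.

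At stake is the SD responder table that Section 17.2.2 promises by dose. Under Section 17.3, SD efficacy is analysed descriptively in the partial database release after the SD phase. Sections 1, 5.1 and 5.4 say the decision on the MD expansion phase uses unblinded safety and efficacy data. SD responder rates may be among those data, although no section says so by name.

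**Working it through.** The protocol gives no figure to reproduce here. The check sets the analysis day against the listed assessment days.

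**Definition.** A subject is a PASI75 responder in the SD phase if (baseline PASI − Day 29 PASI) / baseline PASI ≥ 0.75. PASI90 uses 0.90. Both need a Day 29 score.

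**SD visits and PASI in Section 8.1.1.**

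| SD day | Contact | PASI listed in 8.1.1? |
|---|---|---|
| 1, before dosing | site | yes: "6. PASI and VAS (if applicable") |
| 1 to 2, after dosing | site | yes: "7. PASI and VAS (if applicable") |
| 3 | site | no |
| 8 | site | no (ECG and molecular biomarkers only) |
| 15 | site | yes |
| **29** | **site** | **no** |
| 43 | telephone | no |
| 57 | site | yes |
| 71 | telephone | no |
| 85 | site | yes |
| 106 | site | yes |

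**Could the all-visits list cover Day 29?** It has ten items: vital signs, haematology, biochemistry, urinalysis, hormones, serum/plasma biomarkers, adverse events, local tolerability, concomitant medication and PK samples. PASI is not one of them. The day-specific list has entries for Days 8, 15, 43, 57, 71 and 85 and none for Day 29.

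**Could a visit window cover it?** Section 8.1.1 allows ±3 days from Day 29 on, so the Day 29 visit falls on Days 26 to 32. The PASI days are 1, 2, 15, 57, 85 and 106, and none lies in that range. The nearest are:

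- Day 15, which is 29 − 15 = 14 days earlier.
- Day 57, which is 57 − 29 = 28 days later, or 54 − 29 = 25 days at the early edge of its own window.

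**Comparison with the MD phases.** Section 17.2.2 takes MD PASI75 at Day 57, and Sections 8.1.2 and 8.1.3 both list PASI at Day 57. The mismatch is confined to the SD phase.

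**Number affected.** Section 5.1 plans 24 SD subjects (18 active, 6 placebo). Under Section 8.1.1 alone, scheduled Day 29 PASI values number 0 of 24. The Summary allows one extra cohort per level, to a maximum of 8 subjects, so six doubled levels would give 6 × 8 = 48. A subject who withdraws near Day 29 might have a score from the last-visit procedures (Section 8.1.4), but that is not a scheduled Day 29 measurement.

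**The case against.** The strongest objection concerns Table 2-1. It shares authority with Section 8, and its assessment rows did not survive in the available copy. A PASI mark at Day 29 may stand there, in which case sites might well collect the score. A reader might infer from Section 8.1.1 that no Day 29 PASI is planned anywhere and that the endpoint is certainly lost for every SD subject. The documents do not support that: unreadable rows are not evidence of absence. What does stand is that Section 8.1.1 conflicts with Section 17.2.2 and, if the mark exists, with the flow chart too. Either way, some text has to change.

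The second objection is about weight, and most of it stands. SD efficacy is secondary. Section 17.1 reports no power calculation for the phase, and Section 17.2.2 plans only listings and summaries. With three active subjects and one placebo subject per cohort, a responder rate by dose carries little inferential weight. PASI itself is still listed by time at the other days.

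Two further inferences go too far:

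- **That the gap undermines escalation or the expansion decision.** SD escalation rests on safety and PK through Day 15. The primary expansion endpoint is PASI75 at Day 57, where PASI is scheduled. Sections 1, 5.1 and 5.4 mention efficacy data only in general terms, Section 17.3 mentions only safety data for the expansion decision, and the MD escalation phase supplies its own PASI values.
- **That analysts will pick Day 15 or Day 57 after seeing results.** The protocol describes no such choice. It is fair to say only that it contains no rule for a missing Day 29 score.

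**Conclusion.** The point holds as an internal contradiction. Section 17.2.2 defines SD PASI75 and PASI90 at a visit for which Section 8.1.1 lists no PASI, and no readable part of the protocol resolves it. If sites work from Section 8.1.1, the endpoint cannot be derived as defined for any of the 24 planned SD subjects, apart from a chance score at an early withdrawal. If Table 2-1 marks PASI at Day 29, the loss may not occur in practice, but Section 8.1.1 is then wrong.

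The importance is moderate. One named secondary endpoint and its part in the partial database release are affected. The primary endpoints of all phases and the escalation rules are not. The conclusion assumes that the two procedure lists in Section 8.1.1 are meant to be complete, as the sentence introducing the second list indicates.

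**What to change.** Reconcile Section 8.1.1, Section 17.2.2 and Table 2-1 before first patient first visit (planned for 7 April 2008), because a score not taken at Day 29 cannot be recovered later.

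The preferable change is to add a Day 29 (±3 days) entry to the day-specific list in Section 8.1.1 with BSA, PGA, PASI and VAS (if applicable), and to make sure Table 2-1 shows the same. This keeps the stated endpoint. It also fits Section 6.5, which already uses Day 29 as the SD cut-off for replacing subjects. The cost is one line of text, a check of the flow chart, and one non-invasive skin scoring at an existing visit for 24 subjects, or more if cohorts are added.

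The alternative is to change the SD time point in Section 17.2.2 to a day on which PASI is already scheduled, with the reason for choosing that day stated. This adds no assessment but changes the endpoint, and the protocol gives no basis for preferring one of the listed days over another.

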#### Safety:

- Vital signs (blood pressure, pulse and temperature)
- ECG
- Laboratory safety parameters of haematology, biochemistry, hormones, lipids and urinalysis
- Immunogenicity (antibodies to 109-0012)
- Physical examination

The secondary safety endpoints will be analysed using descriptive statistics.

### **Pharmacokinetics:**

The serum concentration-time data of 109-0012 will be analysed by non-compartmental analysis (NCA). If feasible, the following pharmacokinetic parameters will be derived from these data: Terminal half-life ( $t_{1/2}$ ), maximal observed concentration ( $C_{max}$ ), time to reach maximal concentration ( $t_{max}$ ), accumulation index ( $R_{acc}$ ) area under the curve in the dosing interval ( $AUC_{0-\tau}$ ), area under the curve from time 0 to t ( $AUC_{0-t}$ ) and area under the curve from time 0 to infinity (AUC). The terminal half-life will be calculated as  $t_{1/2} = \ln(2)/\lambda_z$ , where  $\lambda_z$  is the terminal rate constant.  $\lambda_z$  will be estimated as the slope from a linear regression with the natural logarithm to the concentration as the response variable, and time as the explanatory variable. Valid observations from the final part of the curve, which is approximately linear, will be used for the analysis.

Serum concentrations of 109-0012 will be summarised by trial phase and dose and listed by trial phase, dose and subject. The individual as well as the mean concentration-time profiles, by dose will be presented graphically. The pharmacokinetic parameters will be summarised by trial phase and dose and listed by trial phase, dose and subject.

### **Pharmacodynamics:**

Pharmacodynamic biomarker assessments will be analysed using descriptive statistics.

## **17.3 Interim analysis**

After each dose level, the bioanalysis results will be sent electronically (excel-file) for interim PK calculations to the representative in DMPK & Bioanalysis, Novo Nordisk A/S. The preliminary calculation of the PK parameters will be performed after each dose level and will be based on the nominal time points for the dose administration and PK sampling. The serum PK for 109-0012 will be calculated by NCA methods according to current local guidelines. The preliminary pharmacokinetic results will be available at the safety evaluation meetings and will support the dose-escalation decisions during the clinical phase of the trial. The dose escalation decisions will be based on safety and on PK data for all subjects in the current dose cohort through trial Day 15 in the SD dose-escalation phase, and through trial Day 57 in the MD dose-escalation phase. The decision to commence the MD dose-escalation phase will be taken after completion of the third dose level of the SD dose-escalation phase and will be based on safety and PK data for all available subjects. The PK data will be presented in such a manner that unblinding of the Safety Group is avoided.

After completion of the SD dose-escalation phase a partial data base release of the SD dose-escalation phase data will be done and the released data (safety, PK and efficacy) will be analysed using descriptive statistics. Furthermore, after the completion of the SD and MD dose-escalation

phases a decision, based on unblinded safety data will be taken, whether or not the trial should continue into the MD expansion phase. There will also be the possibility to go directly into a phase 2 dose-finding trial.

#### **17.4 Explorative statistical analysis for pharmacogenetics and biomarkers**

These analyses will be planned and performed after trial end when data has been unblinded.

#### **17.5 PK and/or PD modelling**

In addition to the NCA PK evaluation, an exploratory population PK/PD model will be developed. The details of the PK/PD modelling are described in the Modelling Analysis Plan (MAP), which will be prepared before FPFV. Model development will initially be based on interim data. Until data base release, the responsible biomodelling scientist will not take part in Study Safety Group meetings or disclose interim results to any other personnel. After data base release, final models will be created in which all relevant data decisions made at the release meeting have been implemented.

The below list of data will be explored for potential use in the PK/PD-model:

- Serum concentration of 109-0012 at all time points
- Serum concentration of IL-20 at all time points (free as well as amount bound by 109-0012)
- Calculated %neutralisation of serum IL-20 compared to predose IL-20
- Demographic covariates
  - Weight/BMI
  - Sex
- Sub-population: Psoriasis or psoriatic arthritis
- Biochemical assessments
- Pharmacogenomic biomarkers (when available)
- Skin histology
- Efficacy evaluations: PASI score etc. (section [17.2.2.](#))

For validation of the model and exclusion of outliers, please refer to the MAP. The results of the PK/PD model will be reported in a separate Biomodelling report.

## 18 Ethics

This is a first-in-man clinical trial with an antibody having a completely new molecular target, IL-20, a cytokine indicated to be involved in the development of psoriasis. The aim of the trial is to investigate the safety and tolerability of Anti-IL-20 (109-0012) 100 mg/vial after single doses, as well as after four repeated doses, in subjects with psoriasis.

The currently available treatments for moderate to severe psoriasis are all associated with more or less severe side effects. Furthermore many subjects experience loss of efficacy over time as well as rebound effects. Since there is an unmet medical need for safer, more effective and longer lasting treatment effects in subjects with moderate to severe chronic plaque psoriasis, it will be an incentive for subjects to participate in clinical trials which offer a potential benefit.

Pre-clinical safety studies in mice and monkeys have not revealed signs of toxicities with human relevance. Please refer to the IB, 1st Ed, and any updates hereof. However, there is a risk that adverse effects, related to Anti-IL-20 (109-0012) 100 mg/vial administration that have not been identified pre-clinically, can occur in humans. The theoretical adverse events that could potentially be related to administration of the trial product, include injection related events, and adverse events correlated with inhibiting the effect of IL-20, of which the importance to other immune responses are presently unknown.

A rational selection of the starting dose will be made. Thus, the starting dose selection will aim at achieving detectable, but not pharmacological active, concentrations of 109-0012. A cautious dose-escalation principle based on safety data through trial Week 5 will be applied in the SD, dose-escalation phase. In the MD dose-escalation phase a subsequent dose cohort will not be commenced until safety data from 2 weeks after the fourth and last dose have been evaluated, i.e. trial Week 9.

At the termination of the trial, the subject will consult with their Investigator to decide on the best available treatment.

The trial will be conducted in accordance with the Declaration of Helsinki.

### 18.1 Informed consent form for trial subjects

In obtaining and documenting informed consent, the Investigator must comply with the applicable regulatory requirement(s) and adhere to the ICH GCP and the requirements in the Declaration of Helsinki.

Prior to any trial-related activity, the Investigator must give the subject oral and written information about the trial in a form that the subject can read and understand.

A voluntary, signed and personally dated, including time (if necessary), informed consent form will be obtained from the subject prior to any trial-related activity.

The written informed consent must be signed and personally dated, by the person who obtained the informed consent.

If information becomes available that may be relevant to the subject's willingness to continue participating in the trial, the Investigator must inform the subject in a timely manner, and a revised written informed consent must be obtained.

Samples for pharmacogenomic analyses will require a separate written information and informed consent will thus be provided to the subjects for this purpose. It will provide the possibility for the subject to abstain from genetic testing but still be able to participate in the non-genetic part of the trial.

## **18.2 Data handling**

If the subject withdraws the previously given informed consent the subject's data will be handled as follows:

- Data collected will be used as part of the per protocol/intention to treat population.
- Safety events will be reported to International Product Safety, Novo Nordisk /regulatory authorities.

If data is used, it will always be in accordance with local law and subject to IRB/IEC approval.

## **18.3 Institutional review boards/independent ethics committee**

Prior to commencement of the trial, the protocol, any amendments, subject information/informed consent form, any other written information to be provided to the subject, IB, information about payments and compensation available to subjects if not mentioned in the subject information, and other documents as required by the local IRB/IEC should be submitted. The submission letter should clearly identify which documents have been submitted to the IRB/IEC. Written approval/favourable opinion must be obtained from IRB/IEC prior to commencement of the trial.

During the trial, the Investigator must promptly in accordance with local requirements report the following to the IRB/IEC: Updates to IB, unexpected SAEs where a causal relationship cannot be ruled out, substantial amendments to the protocol, non-substantial amendments according to local requirements, deviations to the protocol implemented to eliminate immediate hazards to the subjects, new information that may affect adversely the safety of the subjects or the conduct of the

trial (including new risk/benefit analysis in case it will have an impact on the planned follow-up of the subjects), annually written summaries of the trial status and other documents as required by the local IRB/IEC.

Substantial amendments must not be implemented before approval/favourable opinion, unless necessary to eliminate hazards to the subjects.

The Investigator must maintain an accurate and complete record of all submissions made to the IRB/IEC. The records should be filed in the investigator's trial file and copies must be sent to Novo Nordisk.

#### **18.4 Regulatory authorities**

Regulatory authorities will receive the eIND, substantial/non-substantial amendments to the protocol, IND Safety Reports, and the clinical trial report according to national requirements.

